**Figure 4. F4:**
[figure not shown]
Study schedule. The study schedule describes which intervention and measurements will be measured in which time period. BMI = body mass index, ICU = intensive care unit.

### 2.13. Adverse events

Any acupuncture-related adverse events including minor bleeding, hematoma, infections, alcohol allergy, etc. will be recorded in detail and reported in the study findings. In the event of any serious adverse events the group allocation will be revealed to the patient and the assessors and the patient will receive adequate treatment. The primary investigator and IRB committee will be informed immediately, the IRB committee will determine if the study requires modification or needed to be stopped.

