## 2. Methods

### 2.1. Study design and settings

This single-blind randomized control trial will be implemented in the Department of thoracic surgery of China medical university hospital (CMUH), Taichung City, Taiwan. The study will be initiated on February 2023 and will be concluded until January 2025. This single center study will use a 1:1 ratio parallel group allocation. Informed consent will be obtained prior to the patient’s enrollment. The 2 groups are an intervention group (INT) and a control group (CON). The study was approved by the institutional review board (IRB) of CMUH (approval no. CMUH111-REC3-004) and a study protocol registration online on https://clinicaltrials.gov/ct2/show/NCT05801666 (registration no. NCT05801666). The study aims to examine the effect of acupuncture on preventing and treating dumping syndrome in esophagus cancer patients after feeding jejunostomy surgery. The study will also measure the effect of acupuncture on preventing malnutrition using body weight and body mass index (BMI) (see Fig. 1). In this study, both the patients and the assessors of outcome measurements will be blinded to the group’s allocation.

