### 2.3. Inclusion criteria

Age: 20 to 80-year-old

Advanced esophageal cancer

Post feeding jejunostomy

Plan of Concurrent Chemoradiation Therapy for esophageal cancer

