### 2.7. Randomization and allocation concealment

For study randomization, a 1:1 simple computer-based random number table without stratification was generated via IBM SPSS statistics version 22 (SPSS Inc, Chicago, IL). The 2 groups’ random sequentially number along with correlated acupuncture/sham points picture and name was placed inside 60 nontransparent, sealed envelopes by a study personnel [name]. At the time of intervention, a study research assistant will deliver a random envelope to the acupuncture doctor. The acupuncture doctor will attach the patient’s information to the envelope and will provide the intervention according to the acupuncture/sham points in the envelope.

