**Figure 2. F2:**
[figure not shown]
Acupoints used in the intervention group. Intervention group acupoints: ST36 (Zusanli), ST37 (Shangjuxu), ST39 (Xiajuxu), PC6 (Neiguan), and LI4 (Hegu) liv 3 (Taichung).

As part of the acupuncture procedure, the acupuncturist will disinfect the acupuncture points with 70% alcohol and will insert the needles perpendicularly into the muscle layer at an approximate depth of 10 to 30 mm. The doctor will manipulate the needles upward and downward and will rotate the needles 180° in both directions in a search for the “De Chi” phenomenon. During the intervention, the patient will be positioned in a supine position. After 30 minutes the doctor will withdraw the needles.

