### 2.10. Control group (CON)

The patients in the control group will receive bilateral shallow acupuncture (12 needles) on the sham points that are located 1 cm lateral/medial and 1 cm distal/proximal to the following acupoints: ST36 (Zusanli), ST37 (Shangjuxu), ST39 (Xiajuxu), PC6 (Neiguan), and LI4 (Hegu) liv 3 (Taichung) (Fig. 3). Those points are in a location of 1 cm lateral/medial and 1 cm distal/proximal to those points and are not known as acupuncture points. The needle insertion will be a perpendicular shallow insertion into the skin tissue level. The acupuncture doctor will use the needle with tube insertion for needle insertion and will leave the needle in the depth of the tube insertion (approximately 4 mm depth into the skin) without needle manipulation. The needles will be retained for 30 minutes. In addition to the sham points, the patients in this group will also receive routine Western medicine treatment as per each patient’s needs. The treatment frequency and skin disinfection will be identical to the treatment group.

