### 2.12. Outcome measures

Main outcome measurements are: body weight, BMI (will be measured weekly) dumping syndrome questioners: the Sigstad’s score in order to determine the diagnosis of dumping syndrome and the Arts’ dumping questionnaire in order to assess early or late dumping syndrome (will be measured on the baseline, week 3, week 6) (see Figure S1, Supplemental Digital Content, http://links.lww.com/MD/J34 for the Sigstad’s score and Figure S2, Supplemental Digital Content, http://links.lww.com/MD/J35 for the Arts’ dumping questionnaire).

The secondary outcomes are: muscle grip strength test (measured weekly in kg) (by electronic hand grip test model EH101 manufactured by “CAMRY,” China), blood test: Complete Blood Count, kidney and electrolytes (measured as adjuvant adjuvant concurrent chemoradiation therapy schedule), pre-albumin, albumin level, glucose blood levels, inflammation data including Erythrocyte Sedimentation Rate and C-reactive protein (measured at baseline and on week 6). Total Intensive care unit stay, total hospital stay, and total mechanical ventilation in days will be measured 6 months after inclusion. Mortality will be measured at 3 months, 6 months. Medical charts and drug use will also be measured (Fig. 4). All measurements will be measured by nurses and doctors in the department that are blind to the study group allocation.

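### Section 2.13 commits to recording non-serious adverse events only when they are judged acupuncture-related, so events put down to chemoradiation can go unrecorded and the counts by arm can be distorted

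*Protocol article*

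**What the plan says.** Section 2.13 of the protocol article sets the rule for non-serious events: "Any acupuncture-related adverse events including minor bleeding, hematoma, infections, alcohol allergy, etc. will be recorded in detail and reported in the study findings". For serious events the same section attaches no condition on cause: "In the event of any serious adverse events the group allocation will be revealed to the patient and the assessors", and the principal investigator and the ethics committee are informed at once.

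The setting matters for how the first rule works:

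- Section 2.3 makes this an inclusion criterion: "Plan of Concurrent Chemoradiation Therapy for esophageal cancer".
- The arms differ in physical exposure. In section 2.9 (text after Figure 2) the acupuncturist will "insert the needles perpendicularly into the muscle layer at an approximate depth of 10 to 30 mm" and manipulate them. In section 2.10 the control needles stay at "approximately 4 mm depth into the skin", without manipulation.
- The acupuncture doctor knows the arm, because under section 2.7 this doctor "will provide the intervention according to the acupuncture/sham points in the envelope".
- Section 2.1 states that "both the patients and the assessors of outcome measurements will be blinded to the group’s allocation". Section 2.12 closes with "All measurements will be measured by nurses and doctors in the department that are blind to the study group allocation", but the outcomes listed in that section do not include adverse events.

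**The concern.** The rule asks about cause before an event is written down. That works where the cause is plain. It works poorly where the patient is receiving another treatment that could explain the same event, which is the position of every patient here. An infection, or bleeding away from a needle site, that is put down to chemoradiation does not meet the stated condition for recording, even if needling caused or worsened it.

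Two things are at stake. First, the safety record can be incomplete in both arms. Second, the events will be published from a two-arm trial, so readers will set the arms side by side. If like events are more readily called acupuncture-related in one arm than in the other, the published counts will differ from the true ones, and nothing in the counts would show it.

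**Working it through.** The article states no adverse event rate, no attribution rate and no safety analysis, so there is no figure to reproduce. The check has a textual part and an illustration.

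**Text.** Within section 2.13, the sentence on non-serious events is limited to those related to acupuncture, while the sentence on serious events covers all of them. The filter therefore applies to non-serious events only. Of the four listed examples, haematoma and alcohol allergy can mostly be recognised by place and timing, as can bleeding at a needle site. Infection, and bleeding elsewhere, have a competing explanation in planned chemoradiation. The section names nobody to decide relatedness. The blinding statements in sections 2.1 and 2.12 concern outcome measurements and neither confirm nor exclude a blinded judgement of cause.

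**Illustration.** Inputs: 30 patients per arm (section 2.14). The true event rates and the probabilities that an event is called acupuncture-related are assumptions, varied to show a range.

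Recorded rate = true rate × probability of being called related, in each arm. Expected count = 30 × recorded rate.

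| True rate, deep v shallow | Called related, deep v shallow | Recorded rate | Expected count | Risk difference | Ratio |
|---|---|---|---|---|---|
| 30% v 30% | 100% v 100% | 30% v 30% | 9.0 v 9.0 | 0 | 1.0 |
| 30% v 30% | 50% v 50% | 15% v 15% | 4.5 v 4.5 | 0 | 1.0 |
| 30% v 30% | 70% v 30% | 21% v 9% | 6.3 v 2.7 | 0.12 | 2.33 |
| 30% v 30% | 30% v 70% | 9% v 21% | 2.7 v 6.3 | −0.12 | 0.43 |
| 40% v 20% | 100% v 100% | 40% v 20% | 12.0 v 6.0 | 0.20 | 2.0 |
| 40% v 20% | 50% v 50% | 20% v 10% | 6.0 v 3.0 | 0.10 | 2.0 |
| 40% v 20% | 70% v 30% | 28% v 6% | 8.4 v 1.8 | 0.22 | 4.67 |
| 40% v 20% | 30% v 70% | 12% v 14% | 3.6 v 4.2 | −0.02 | 0.86 |

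Sample line, last row: 0.40 × 0.30 = 0.12 and 0.20 × 0.70 = 0.14; 0.12 − 0.14 = −0.02; 0.12 / 0.14 = 0.86.

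The pattern is general. Whenever fewer than all events are called related, events are lost. With equal attribution in both arms the ratio is kept, but any true difference shrinks in proportion. The ratio is distorted only when attribution differs by arm, and that can create a difference, enlarge it, hide it or reverse it. If events are recorded whatever their cause, attribution drops out of the calculation and the first row of each block applies.

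**The case against.** The case on the other side is substantial, and much of it stands.

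- *The section does not say that other events will go unrecorded, and this is a condensed article.* That is a fair answer on who judges relatedness, a detail that an article commonly leaves to the full protocol; its absence is no fault in itself. It does not answer the scope of recording, which the article does fix.
- *No safety comparison between the arms is planned.* Correct. The aims, hypothesis and outcome sections contain none. A reader might infer that a planned safety comparison is biased, but the document does not support that. What can be distorted is the set of counts reported by arm.
- *Judgement by someone who knows the arm is not stated.* Correct. A reader might infer that the acupuncture doctor will decide relatedness, since this doctor attends the sessions. No section says so, and blinded staff exist who could do it. Hence the counts can be distorted; it is not established that they will be.
- *The listed events are mostly local to the needle.* Largely true, which confines the problem chiefly to infection and to bleeding away from a needle site.
- *Unrecorded events could be recovered.* In part. Section 2.12 collects medical charts, drug use, blood counts and inflammation markers, so it would be wrong to call the events irrecoverable. No adverse-event use of these sources is stated, however, and minor events may not be charted.
- *Serious events are escalated whatever the cause.* True, so the most consequential bleeding or infection does not pass through this filter.
- *The trial is too small to compare such events anyway.* With 30 per arm, power to separate 40% from 20% is about 39%, and 20% from 10% about 19%. The counts will be descriptive at best. That is a reason to expect little from a test, not a reason to record incompletely.

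**Conclusion.** The point holds in a limited form. Section 2.13 commits to recording non-serious adverse events only when they are acupuncture-related, in patients whose other treatment can explain some of the same events. Followed as written, the rule can lose ambiguous events in both arms. If attribution differs by arm, it can also move the reported counts for deep and shallow needling in either direction.

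The size cannot be determined from the document. The illustrated ratios, from 0.43 to 2.33 where the true ratio is 1.0 and from 0.86 to 4.67 where it is 2.0, rest entirely on assumed event rates and on assumed attribution of 30% to 70%. They show what the rule permits and do not predict what will happen. No efficacy outcome and no sample size figure is affected. This is a worthwhile and inexpensive improvement to a stated rule.

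**What to change.** Reword section 2.13 so that all bleeding, haematoma, infection and skin reactions are recorded in both arms, from the first session to week 6, whatever the suspected cause. Have them collected by the blinded nurses and doctors of the department, who already see patients weekly for body weight and grip strength. Report these events by arm. Record relatedness as a separate field, completed by someone who does not know the arm; for a patient whose allocation has been revealed after a serious event, this must be someone who has not been told.

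The cost is one change of wording, one extra field on the form and more entries, many of which should already be in the charts that the trial collects. The safety table will also contain background events due to chemoradiation. Treatment, sample size and the efficacy analysis are unchanged.

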Limitations of the study include a specific Taiwanese population and cannot be generalized to other populations. This study is also only a single-center study. The study protocol could not apply a double-blind design due to the type of intervention (manual acupuncture). The study will investigate the role of acupuncture in the prevention of dumping syndrome and malnourishment, the study does not require a positive Sigstad’s score to verify dumping syndrome as a condition for inclusion, therefore it is possible that the number of patients that will develop dumping syndrome could be low, in this case, the study will focus on body weight and BMI as the main outcomes to assess the prevention of malnourishment. The study did not specify the cancer stage in the inclusion criteria. High mortality rates in Esophagus cancer might impair the completeness of the data and can increase the levels of missing data.

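### The serious-adverse-event rule reveals allocation to outcome assessors, which undercuts the promised blinding of the week 3 and week 6 dumping questionnaires

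*Protocol article*

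**What the plan says.** Section 2.1 of the protocol article sets the blinding: "both the patients and the assessors of outcome measurements will be blinded to the group’s allocation". Section 2.12 repeats it for every outcome and says who the assessors are: "All measurements will be measured by nurses and doctors in the department that are blind to the study group allocation".

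Section 2.13 then gives the unblinding rule: "In the event of any serious adverse events the group allocation will be revealed to the patient and the assessors". The same sentence adds that the patient will be treated, and the next one has the investigator and the IRB informed and the IRB decide whether the study is modified or stopped. The sentence before the rule concerns a narrower class of events: "Any acupuncture-related adverse events including minor bleeding, hematoma, infections, alcohol allergy, etc. will be recorded in detail and reported in the study findings".

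The Sigstad score and the Arts questionnaire are main outcomes, taken at baseline, week 3 and week 6 (Section 2.12).

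**The concern.** Emergency unblinding is normal. What is unusual is a standing instruction to tell the people who rate the outcomes, whatever the event and whether or not they need to know. The acupuncturist cannot be blinded, as the Discussion acknowledges, so the blinding of patients and assessors is the trial's protection against biased ratings.

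At stake is the comparison of the two dumping questionnaires, on which the hypothesis in the Introduction rests. Once the assessor knows the arm, later ratings for that patient are open-label. The loss does not fall at random: it follows an event after randomization that is tied to prognosis and possibly to treatment. Nothing in the rule separates those managing the event from those scoring the questionnaires.

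**Working it through.** The article states no figure on this point, so the main check is a reading of the text. The arithmetic in step 4 only gives scale.

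**1. Scope of the rule.** Sections 2.1 and 2.12 promise blinded assessors without exception. Section 2.13 makes an exception triggered by any serious event. The limit to acupuncture-related events stands in the preceding sentence, where it governs recording and reporting, and the unblinding sentence does not repeat it. As written, a serious event caused by the cancer or by chemoradiation also triggers disclosure.

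**2. Can the trigger occur in this population?** The inclusion criteria in Section 2.3 include "Advanced esophageal cancer" and "Plan of Concurrent Chemoradiation Therapy for esophageal cancer". The Discussion warns: "High mortality rates in Esophagus cancer might impair the completeness of the data and can increase the levels of missing data". Serious events are therefore foreseeable, but no rate is given, and none for the first six weeks in particular.

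**3. Which ratings are exposed?** Three conditions must hold together: the event comes before week 3 or week 6, the patient is still assessed afterwards, and the outcome leaves room for judgement or for the patient's account.

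- Sigstad and Arts at weeks 3 and 6: exposed.
- Weight, BMI, grip strength read from an electronic device, laboratory values, mortality: little exposed.
- Any questionnaire after a death, or any event after week 6: no effect on the questionnaires.

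**4. Scale, under assumptions.** Inputs: 60 patients, 30 per arm (Section 2.14), and an assumed event rate *p* before week 6.

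Expected number told = 60 × *p*; chance of at least one = 1 − (1 − *p*)^60.

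| Assumed *p* | Expected number told | Chance of at least one |
|---|---|---|
| 5% | 60 × 0.05 = 3 | 95% |
| 10% | 60 × 0.10 = 6 | 99.8% |
| 20% | 60 × 0.20 = 12 | above 99.9% |
| 40% | 60 × 0.40 = 24 | above 99.9% |

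These are ceilings for the questionnaires, because some of these patients will not be rated again.

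For possible bias, let *u* be the share of rated patients in each arm whose rating follows disclosure. Suppose those ratings shift by *b* standard deviations, upward in one arm and downward in the other. The spurious standardized difference is *d* = 2 × *u* × *b*. The false-positive rate is that of a two-sided 5% *t* test with 30 per arm (noncentral *t*) when the true difference is zero.

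| *u* | *b* | *d* = 2*ub* | False-positive rate |
|---|---|---|---|
| 10% | 0.25 | 0.05 | 5.4% |
| 10% | 0.50 | 0.10 | 6.7% |
| 20% | 0.25 | 0.10 | 6.7% |
| 20% | 0.50 | 0.20 | 11.9% |
| 40% | 0.25 | 0.20 | 11.9% |
| 40% | 0.50 | 0.40 | 33.2% |

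Both *u* and *b* are assumed. Shifts in opposite directions are an unfavourable case. At low shares the effect is slight; it becomes material only if many patients are told and still rated.

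**The case against.** The strongest reply is that the authors meant serious events caused by the needling. Section 2.13 opens with acupuncture-related events, and it would be odd for every chemoradiation admission to prompt an immediate IRB decision on stopping the study. On that reading few patients would be unblinded. This stands as a limit on size. It does not rescue the wording, which says any serious event, and even a needling-related event gives no evident reason to tell someone whose only role is to score a questionnaire.

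It can also be said that unblinding is an ordinary exception to a general rule, so that Section 2.13 does not strictly contradict Sections 2.1 and 2.12, and that logs and sensitivity analyses may sit in documents not shown. Both are fair. The point rests on what the article orders, not on what it leaves out.

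The assessors are department nurses and doctors and may also treat the patient, so some may properly need the allocation. This stands, and it rules out requiring that every assessor stay blind in every case.

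A reader might go further in three ways that the article does not support:

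- **Outcomes as evidence of early events.** ICU stay, ventilation and hospital stay are totalled at 6 months and mortality at 3 and 6 months. They do not show how many events fall before week 6, and a patient who has died yields missing data, not a biased rating.
- **Spill-over to other patients.** Section 2.7 describes simple randomization with sealed envelopes, so one patient's allocation tells staff essentially nothing about another's.
- **Damage to all main outcomes.** Weight and BMI are also main outcomes, are hard to bias, and become the focus if few patients develop dumping syndrome (Discussion).

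**Conclusion.** The point holds in a limited form. Section 2.13 orders disclosure to outcome assessors without a condition on relatedness or need to know, and so undercuts the assessor blinding in Sections 2.1 and 2.12. The harm is confined to Sigstad and Arts ratings at weeks 3 and 6, in patients who have already had a serious event and are still assessed.

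Its size cannot be fixed. The article does not support a claim that a substantial share of patients will lose assessor blinding, although the number is unlikely to be zero if the rule is applied literally and the event rate is 5% or more. If only acupuncture-related events are meant, it would be small. The tabulated false-positive rates illustrate a mechanism and do not forecast this trial.

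This is a defect that should be corrected because the remedy is cheap. It does not invalidate the design. The patient is told as well, which matters for symptom questionnaires and is a reason to examine post-disclosure ratings whoever made them.

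**What to change.** - **Reconcile the text.** Bring Section 2.13 into line with Sections 2.1 and 2.12 by removing routine disclosure to outcome assessors. The allocation goes only to those who need it to manage or oversee the event. State whether the trigger is any serious event or only acupuncture-related ones. Leave the patient-care wording unchanged.
- **Reassign where roles overlap.** If a department nurse or doctor learns the allocation because they also treat the patient, another member of the existing pool who is still blind does that patient's remaining Sigstad and Arts assessments.
- **Log.** Record each unblinding with arm, date and the roles told, and report the counts by arm.
- **Sensitivity analysis.** Repeat the Sigstad and Arts comparisons with ratings made after unblinding set aside. This also covers visits at which only the patient had been told. It selects on a post-randomization event, so it should sit beside the main analysis and not replace it.

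The cost is a short text change, a small log, an occasional change of assessor and one extra analysis. Whether the pool always has a blinded colleague free is for the site to confirm.
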